### Concealment mechanism {16b}

Randomization will be performed using the eCRF module in RedCap® that is preloaded specifically for this study prior to its initiation. This module allows for efficient and accurate random assignment of participants to their respective treatment groups.

### Implementation {16c}

Participants will be recruited by the clinical staff involved in the study, and the informed consent process will be conducted by the principal investigator or a designated delegate, following the established procedures at the San Ignacio University Hospital. Once participants have signed the consent form, if applicable, the pharmacist will assign them to either the placebo or intervention group for dispensing. The blinding of the study will be maintained until all participants have been assigned to their respective groups, and it will only be opened by designated personnel responsible for the analysis of the results at the conclusion of the study.

## Assignment of interventions: Blinding

### Who will be blinded {17a}

In Phase I, both the patients and the members of the research team are aware that the patients are receiving the research phytomedicine, Esperanza. However, in Phase II for gastric tumors, a double-blind approach will be implemented. This means that both the patients and the members of the research team, except for the pharmacist, will be unaware of whether the patients are receiving the placebo or the intervention. The pharmacist, being the only non-blind staff member, will have knowledge of the assigned treatments for dispensing purposes.

### Procedure for unblinding if needed {17b}

In the event of serious adverse events that, in the opinion of the Principal Investigator, require unblinding (such as high severity, unexpected events possibly related to the study drug), the pharmacist will request the unblinding process. The pharmacist will consult the treatment assignment list and inform the Investigator of the assigned treatment for the patient through email. The unblinding process will be documented in the electronic medical record, RedCap, and will be officially notified to the Sponsor and the Ethics Committee (CIEI), including the date and the reason for the unblinding. Monitors with access to unblinded records will be able to verify that the dispensing was conducted in accordance with the randomization scheme for quality assurance purposes.

## Data collection and management

### Plans for assessment and collection of outcomes {18a}

All participants in the clinical trial will undergo scheduled evaluations as outlined in the study protocol. To ensure smooth coordination of these activities, a dedicated coordinator from the research center will be responsible for organizing and overseeing the necessary procedures. Additionally, prior to the commencement of the study, all team members will receive comprehensive training to familiarize themselves with the protocols and ensure the accuracy and validity of the results. The administration of scales and evaluations will strictly adhere to the established procedures to maintain consistency and reliability throughout the study.

### Plans to promote participant retention and complete follow-up {18b}

At the outset of enrollment, all participants are thoroughly informed about the significance of adhering to the instructions and recommendations provided by the research team. They are encouraged to raise any questions or concerns they may have and assured of continuous support through regular telephone communication and follow-up visits. In cases where a patient fails to attend scheduled visits, the research team will proactively reach out to their relatives to ascertain the reason for the absence and aid ensure compliance with the planned visits. This proactive approach aims to maintain the continuity and completeness of the study data while prioritizing the well-being and engagement of the participants.

### Data management {19}

A electronic case report form (eCRF) will be completed for each selected and enrolled subject in the study. The eCRF data will be captured using an electronic data capture system (CED), specifically designed by the statistics and epidemiology section of the Research Center at Hospital Universitario San Ignacio in RedCap ®. The investigator will maintain subject files where all subject data will be documented. These files serve as the primary source of data for the study. The research center staff will accurately record all required eCRF data specified in the protocol within the system. All data entered into the eCRF will be supported by corresponding source documentation.

If necessary, the investigator or an authorized member of the investigator's team will make any required corrections to the eCRF. The audit trail, an integral part of the system, will record all modified information, including the date and person responsible for the correction. Periodic reviews of the eCRFs will be conducted by CRO staff to ensure completeness, legibility, and compliance. Access to all source documents pertaining to the study will be granted to verify the accuracy of data entered the eCRF. The Principal Investigator will review the eCRFs for completeness and accuracy, electronically signing and dating them as confirmation of their review.

### Confidentiality {27}

The information generated during this clinical study is deemed confidential and will be utilized solely for the purposes related to the development of Esperanza extract. This confidential information will remain the exclusive property of the sponsors and shall not be disclosed to any third parties without written consent. It is strictly prohibited to use this information for any purpose other than the proper execution of this study. Additionally, the personal data of the participants will be kept confidential and will not be disclosed at any point during or after the study. Proper anonymization measures will be implemented to ensure the protection of participants' privacy.

### Plans for collection, laboratory evaluation and storage of biological specimens for genetic or molecular analysis in this trial/future use {33}

N/a: The collection of all data and biological samples for this study is an integral part of the protocol activities. After completing analysis, samples will be discarded following standardized hospital protocol.

## Statistical methods

### Statistical methods for primary and secondary outcomes {20a}

A descriptive analysis of the study database will be conducted, including measures of central tendency (such as mean, median, and mode) and dispersion (such as standard deviation and range) for quantitative variables, as well as frequencies and counts for categorical/ordinal variables. In cases where data is missing, an active search will be performed in the electronic clinical record system (SAHI®) of the Hospital, clinical laboratory database (LabCore®), and directly from the patient to retrieve the missing information.

No imputation method is expected to be used, and only patients with complete information will be included in the analysis for each specific objective. For exploratory analyses, the normality of each quantitative variable will be assessed to determine the appropriate use of statistical tests. Depending on the distribution of the data, parametric tests such as the Student's t-test and ANOVA may be used for comparisons between groups, while non-parametric tests such as the Kruskal–Wallis and Mann–Whitney test may be used for non-normally distributed data. The Logrank test will be utilized for survival outcomes associated with that objective.

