**Methods:**

This is a prospective, open label, phase I/ randomized, double-blind single-center phase II study designed to evaluate the safety and efficacy of Esperanza extract in patients with metastatic gastrointestinal tumors and acute leukemias. In stage 1, the study will determine the MTD and assess safety. In stage 2, safety at the MTD will be evaluated, and the efficacy of Esperanza extract will be explored in both metastatic gastric tumors and acute leukemias. Quality of life improvement will be the primary outcome in the gastric tumor group, while different efficacy outcomes will be assessed in the acute leukemia group. A placebo group will be used for comparison in the gastric tumor group, and a historical control group will be used in the acute leukemia arm.

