**Efficacy Assessment**					
RECIST		X			X
Tumor Antigens		X			X
CA199		X			X
ACE		X			X
Metabolome		X		X	X
Microbiome Analysis		X			X
Proinflammatory Cytokines		X		X	X
Circulating DNA		X		X	X
Ketone Bodies		X		X	X
Tumor Infiltration		X			X
QLQ C-30 Quality of Life Surveys		X	X	X	X
Progression-Free Survival		X			X

For newly diagnosed acute leukemias, a total of 28 new patients will be recruited, and an additional six patients will be recruited for the relapsed leukemias group. Both groups will receive continuous treatment with the Esperanza extract at the determined MTD for four weeks. Standard chemotherapy treatment for their underlying disease will be administered to both groups. At the end of the treatment cycle, safety and efficacy evaluations will be conducted. Table 3 provides a comprehensive list of the activities to be carried out during the patients' intervention.

**Table 3 Tab3:** Activity schedule for phase II clinical trial in acute leukemias

Schedule of activities				

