### Participant timeline {13}

#### Sample size {14}

For phase I, a sample size of 6 patients was determined for gastric tumors and acute leukemias. In case of presentation of any adverse event in the first in these patients, the dose will be decreased for the second cycle; in case of an adequate safety profile, the dose will be doubled for the second cycle.

The sample sizes for phase II were determined for both gastrointestinal tumors and hematologic tumors. For gastrointestinal tumors, a sample size of 30 patients was calculated, with 15 patients per group, considering a mean difference of at least 6 points in quality of life, a standard deviation of 5 and 6 points for each group, an alpha error of 0.05, and a beta error of 0.20. Additionally, a 10% allowance was added for possible study losses. For hematologic tumors, the sample size calculation was based on response criteria such as improvement, remission rate, and hematologic recovery. The ANOVA test was used, an alpha error of 0.05, a beta error of 0.20, and an effect size of 0.4. The resulting sample size was 28.

It should be noted that these sample sizes will be reassessed at the end of phase I for both gastric tumors and acute leukemia. The recalculated sample size for phase I/II is 36 for gastrointestinal tumors and 46 for hematologic tumors.

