## Assignment of interventions: allocation

### Sequence generation {16a}

During the screening visit, all participants will be assigned a unique subject number in sequential order (e.g., 001, 002, 003, etc.), which will remain consistent throughout the study. The treatment chosen by the attending physician will be administered to all participants, without randomization in phase I.

In phase II, patients with gastrointestinal tumors will undergo randomization using a specially designed application within the eCRF in RedCap®. The randomization will be conducted using a simple non-stratified approach, predetermined, and loaded into the eCRF for the pharmacist, who will be unblinded. Randomization will not be employed for acute leukemias, as the comparison of outcomes will be conducted against a historical group using propensity score matching.

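### QLQ-C30 is collected at the initial visit, but the tests named for the 15-per-arm quality-of-life comparison carry no baseline covariate; prespecified ANCOVA would usually be more precise

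*Protocol article*

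**What the plan says.** The abstract of the protocol article states: "Quality of life improvement will be the primary outcome in the gastric tumor group". Table 2, under Efficacy Assessment, has a row "QLQ C-30 Quality of Life Surveys" marked at the initial visit (Week 2), cycle 2 (Week 6), cycle 3 (Week 10) and close-out (Weeks 12-14). A score from the start of treatment is therefore planned for every patient.

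Sample size {14} sizes this part as a comparison of two means: "considering a mean difference of at least 6 points in quality of life", "a standard deviation of 5 and 6 points for each group", and "an alpha error of 0.05, and a beta error of 0.20. Additionally, a 10% allowance was added for possible study losses". The result is 15 per group. No correlation between the initial and later scores enters the calculation.

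Sequence generation {16a} adds: "The randomization will be conducted using a simple non-stratified approach".

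Statistical methods {20a} offers, after a normality check, "parametric tests such as the Student's t-test and ANOVA may be used for comparisons between groups", with the Mann-Whitney and Kruskal-Wallis tests for non-normal data and the logrank test for survival. The tests are given as examples and permissively, and the sentence that introduces the normality check refers to exploratory analyses. The section heading nevertheless covers primary and secondary outcomes, and no other method for QLQ-C30 appears in the article.

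**The concern.** None of the named tests takes a baseline covariate. Allocation does not balance baseline quality of life either, because it is simple and unstratified across colon, pancreas, stomach and bile duct tumours. If initial and later scores are correlated, an unadjusted comparison of follow-up scores leaves in the error term variation that the collected data could remove. Any chance difference between the arms at the start then carries through to the observed treatment difference in proportion to that correlation.

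With about 30 patients this matters in two ways. The margin over the planned 80% power is thin, and it disappears once the planned losses occur under the complete-case rule. And if an imbalance is seen and adjusted for afterwards, the adjustment becomes a data-driven choice. Naming the model in advance avoids both problems.

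**Working it through.** **Inputs.** From Sample size {14}: difference 6, SDs 5 and 6, alpha 0.05, power 80%, losses 10%, 15 per arm. Assumed: a two-sided test (not stated), and rho, the correlation between initial-visit and follow-up scores (not given, so shown as a range).

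**The plan's own figure.** n per arm = (1.960 + 0.842)² × (25 + 36) / 6² = 13.3. Allowing for 10% loss, 13.3 / 0.9 = 14.8 or 13.3 × 1.1 = 14.6. Both round up to 15 per arm, so the stated 30 reproduces.

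**Unadjusted t-test.** SE = √(61/n), df = 2n − 2, noncentral t.
- n = 15: SE = 2.017, noncentrality 6 / 2.017 = 2.975, power 81.9%.
- n = 13.5 (10% loss): SE = 2.126, noncentrality 2.823, power 77.4%.

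**ANCOVA, if SDs 5 and 6 describe follow-up scores.** SE = √(61/n × (1 − rho²) × (1 + 1/(2n − 4))), df = 2n − 3. The last factor allows for chance baseline imbalance when the slope is estimated. At n = 15 and rho = 0.5: SE = 2.017 × √(0.75 × 1.0385) = 1.780, noncentrality 3.371, power 90.1%.

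| Assumed rho | Power, n = 15 | Gain over 81.9% (points) | Power, n = 13.5 | Gain over 77.4% (points) |
|---|---|---|---|---|
| 0.2 | 81.9% | 0 | 77.2% | 0 |
| 0.3 | 83.9% | 2 | 79.4% | 2 |
| 0.4 | 86.7% | 5 | 82.4% | 5 |
| 0.5 | 90.1% | 8 | 86.4% | 9 |
| 0.6 | 94.0% | 12 | 91.2% | 14 |
| 0.7 | 97.6% | 16 | 96.0% | 19 |

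A simulation of 20,000 trials with SDs 5 and 6, n = 15 and rho = 0.5 gave 81.6% for the t-test and 90.0% for ANCOVA.

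**ANCOVA, if SDs 5 and 6 describe change scores.** With equal SD s at both visits, the variance of change is 2s²(1 − rho) and the ANCOVA residual variance is s²(1 − rho²). The ratio is (1 + rho)/2, which replaces (1 − rho²) above.

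| Assumed rho | Power, n = 15 | Gain over 81.9% (points) | Power, n = 13.5 | Gain over 77.4% (points) |
|---|---|---|---|---|
| 0.3 | 93.7% | 12 | 90.8% | 13 |
| 0.5 | 90.1% | 8 | 86.4% | 9 |
| 0.7 | 86.3% | 4 | 82.0% | 5 |

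The ordering reverses: under this reading a stronger correlation means a smaller gain.

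**Interval width.** At n = 15 the unadjusted 95% half-width is 2.048 × 2.017 = 4.13 points. With ANCOVA at rho 0.5 it is 2.052 × 1.780 = 3.65 points (3.58 without the imbalance factor).

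**Chance imbalance.** The SE of the baseline mean difference at 15 per arm is √(2/15) = 0.37 SD. A difference above 0.5 SD in either direction has a probability of about 17%. If the baseline SD equals the pooled √(61/2) = 5.52 (an assumption), one SE is 2.0 points. At rho 0.5 that shifts an unadjusted follow-up comparison by about 0.5 × 2.0 = 1.0 point, against a target of 6.

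**The case against.** The strongest reply is that nothing here is wrong against the plan. The sample size was set for an unadjusted two-mean comparison, N = 30 reproduces, and the power is 81.9% if all 30 are analysed. Randomisation protects the type I error whatever the baseline imbalance. The size is also to be recalculated after phase I. All of this stands: the loss is relative to ANCOVA, not to the planned 80%. Only with planned losses does t-test power fall to 77.4%.

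A reader might infer that the article commits the trial to an unadjusted test that ignores the baseline and so loses 8 to 9 points of power. The documents do not support that. The wording of {20a} is permissive. The abstract speaks of improvement, so a t-test on change from baseline, which does use the initial score, is open. The statement that no additional analysis is planned ({20b}) concerns analyses such as subgroups and does not bar a covariate in the primary model. The 8-to-9-point figure needs rho near 0.5, and no correlation is given.

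It can also be said that the choice of covariate belongs in an analysis plan that is not shown. That is fair for an omission. Here, though, the article does name a family of tests under the primary-outcome heading, and its sample size matches that family, so the choice can be reviewed as written. The change-score reading does not remove the point either: for rho between 0.3 and 0.7, ANCOVA gains power under both readings.

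**Conclusion.** The point holds as a recommendation to use a better method on data already being collected; it is not an error that invalidates the planned comparison. At 15 per arm the gain in power is about 0, 2, 5, 8, 12 and 16 points at assumed rho 0.2, 0.3, 0.4, 0.5, 0.6 and 0.7 if the stated SDs are for follow-up scores, and about 12, 8 and 4 points at rho 0.3, 0.5 and 0.7 if they are for change scores. This rests on a two-sided test, the plan's difference and SDs, an assumed rho, and an initial-visit score that is a true pre-treatment value. That last condition is not stated: Table 2 puts the initial visit, chemotherapy cycle 1 and dispensing in the same column. On follow-up scores with rho about 0.2 or lower, the gain is negligible.

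**What to change.** In {20a}, name the primary gastrointestinal phase II analysis as ANCOVA of the close-out QLQ-C30 score on treatment group, with the initial-visit score as covariate, and report the adjusted mean difference with its 95% CI. State that the initial-visit questionnaire is completed before the first dose. Keep the unadjusted t-test or Mann-Whitney test as a sensitivity analysis. In {14}, say whether SDs 5 and 6 refer to follow-up or change scores. Outcomes {12} places the quality-of-life evaluation at 4 to 6 months, while Table 2 ends at Weeks 12-14; the two should be reconciled so that the analysed time point is unambiguous.

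A mixed model on all post-baseline scores with the baseline score as covariate is an alternative, but not an equivalent one, because its estimand and its handling of missing visits differ.

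The cost is a few sentences of text and one degree of freedom, with no new patients, visits or data.

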### Interim analyses {21b}

At the end of phase I, an analysis of the safety profile will be conducted to evaluate the adverse events and determine if any additional safety tests or measures need to be implemented in phase II. This analysis will provide valuable insights into the safety and tolerability of the intervention.

Based on the initial results from phase I, the sample size for phase II will be recalculated, taking into consideration the outcomes observed during phase I. This recalculation aims to ensure an appropriate sample size that allows for robust statistical analysis and meaningful conclusions in phase II.

### Methods for additional analyses (e.g. subgroup analyses) {20b}

N/a: No additional analysis is planned.

### Methods in analysis to handle protocol non-adherence and any statistical methods to handle missing data {20c}

In cases where data is missing, an active search will be performed in the electronic clinical record system (SAHI®) of the Hospital, clinical laboratory database (LabCore®), and directly from the patient to retrieve the missing information. No imputation method is expected to be used, and only patients with complete information will be included in the analysis for each specific objective.

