### Objectives {7}

The main goal of phase I is to assess the safety, toxicity, and maximum tolerated dose (MTD) of the Esperanza extract in patients diagnosed with metastatic gastric tumors and acute leukemias. In phase II, the focus shifts to evaluating the safety of the extract and examining its impact on improving patients' quality of life using the QLQ-C30 scale for gastric tumors. Additionally, in the context of acute leukemias during phase II, the emphasis remains on determining the safety of the extract and investigating its potential to enhance the rate of remission during induction therapy and/or facilitate hematological recovery.

In addition to the primary objectives, there are important secondary objectives for gastric tumors. One of these is to evaluate the influence of the Esperanza extract on progression-free survival and clinical response, which will be assessed using the RECIST 1.1 criteria. For acute leukemias, the assessment will focus on event-free survival, defined as the duration from enrolment to disease progression, including local or distant recurrence, second primary malignancy, primary malignancy-related death, or death from any cause, whichever comes first. Furthermore, a thorough evaluation of the impact on patients' quality of life will also be conducted.

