### Intervention description {11a}

#### Phase I treatment:

Patients who meet the inclusion criteria and have metastatic gastrointestinal tumors (colon, pancreas, stomach, and bile ducts) or newly diagnosed acute leukemias will initiate treatment with 1000 mg of Esperanza extract daily, divided into two doses of 500 mg, for a duration of 4 weeks. In the event of toxicity, the dose level will be adjusted accordingly. If toxicity occurs, the next dose level will be reduced to 500 mg using the same dosing schedule, and if there is no toxicity after 4 weeks, the dose will be increased to 2000 mg. This dose adjustment will be conducted with the same group of patients, both for escalation and de-escalation, who have completed the previous dose level, ensuring a total treatment duration of 8 weeks. The administration of the phytomedicine Esperanza will continue throughout the intervention period, without interruption, for the entire 8-week treatment duration, unless there is clinically significant toxicity that meets the investigator's criteria for discontinuing the intervention. Table 1 provides a comprehensive list of the activities to be carried out during the patients' intervention.

**Table 1 Tab1:** Schedule of activities for phase ib to evaluate safety and MTD in gastrointestinal tumors and acute leukemias

Schedule of activities				
	**Enrollment**	**Initial Visit and chemotherapy cycle 1**	**Cycle 2**	**Close-out**
**Time point**	**Week 1**	**Week 2**	**Week 6**	**Week 7**
Enrolment				
Screening and Informed Consent	X			
Physical Examen		X	X	X
Clinical Record		X	X	X
HIV Test and Pregnancy test	X			

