#### Phase II treatment:

For patients with metastatic gastrointestinal tumors (colon, pancreas, stomach, and bile ducts), a total of 30 new patients will be enrolled and divided into two groups: an intervention group and a placebo group, each consisting of 15 patients. The intervention group will receive continuous treatment with the Esperanza extract at the determined maximum tolerated dose (MTD) for three treatment cycles, equivalent to approximately 12 weeks. The placebo group will receive a placebo in addition to standard chemotherapy treatment for their underlying disease. Safety evaluations will be conducted at the end of each treatment cycle, and the efficacy evaluation will be carried out after completion of the three treatment cycles. Table 2 provides a comprehensive list of the activities to be carried out during the patients' intervention.

**Table 2 Tab2:** Activity schedule for phase II clinical trial in gastrointestinal tumors

Schedule of activities					

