### Criteria for discontinuing or modifying allocated interventions {11b}

Each subject retains the right to voluntarily withdraw from the study treatment at any given time. Moreover, the investigator holds the authority to suspend a subject from the study treatment if deemed necessary for various reasons, such as the occurrence of adverse events or non-adherence to the study protocol. Instances where a subject may be withdrawn from the study treatment include: withdrawal of consent by the subject or their legally acceptable representative, experiencing unacceptable toxicity (grade ≥ 3) with the combination of Esperanza and standard therapy according to NCI CTCAE version 5.0, as well as cases where the investigator determines the toxicity to be clinically intolerable. Additionally, suspension may occur if there is a clinically significant elevation that falls below grade 3 or 4, at the discretion of the investigator. Significant non-compliance with the protocol that could jeopardize the subject's safety or compromise data integrity also warrants withdrawal. The investigator may also make the decision to withdraw a subject if it is believed to be in the subject's best interest. Lastly, a positive pregnancy test will result in immediate withdrawal from the study treatment.

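### The complete-information rule covers every objective, so read literally it can drop patients who stop early, including for toxicity, from the safety analyses

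*Protocol article*

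**What the plan says.** The rule appears in two places of the protocol article. Section 20a has "No imputation method is expected to be used, and only patients with complete information will be included", and section 20c repeats it: "only patients with complete information will be included in the analysis for each specific objective". Both sections first provide for an active search of the hospital record, the laboratory database and the patient. Neither defines complete information or names an objective to which the rule does not apply.

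Safety is such an objective. Section 7 makes it part of the main goal of phase I and says "In phase II, the focus shifts to evaluating the safety of the extract" for the next stage. Section 12 includes it in the primary outcome. Section 21b plans that at the end of phase I "an analysis of the safety profile will be conducted to evaluate the adverse events", without saying which patients enter.

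Early stopping is foreseen. Section 11b has a list that opens "Instances where a subject may be withdrawn from the study treatment include" and includes toxicity of grade 3 or higher and toxicity the investigator finds intolerable. It does not say whether scheduled tests continue afterwards. Section 14 allows for losses in the gastrointestinal calculation: "Additionally, a 10% allowance was added for possible study losses".

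**The concern.** A complete-case rule may be defensible for a quality-of-life score. It suits safety badly, because the event of interest can itself cause the later data to be missing. A patient who stops because of toxicity is the one most likely to miss the later tests, and is also the one whose experience the safety analysis exists to report.

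The end-of-phase-I analysis decides whether phase II needs further safety tests or measures (section 21b), and safety leads the phase II objectives. If early stoppers are left out, the reported result depends on who stopped: leaving out patients with toxicity lowers the proportion, and leaving out patients without it raises the proportion. Since complete information is undefined, the choice could also be made after the events are known. Phase I and the leukaemia cohorts have no blinding to protect that choice.

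**Working it through.** **What can be missing.** The schedules of activities give the following:

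- Phase I (Table 1): 17 safety tests at weeks 2, 6 and 7 (the echocardiogram row is empty). A patient who leaves before week 6 can have one of three sets.
- Phase II (Tables 2 and 3): 18 safety tests, at the initial visit and close-out only. A patient who leaves before close-out can have no set of these tests after the initial visit. The text for the gastrointestinal part says "Safety evaluations will be conducted at the end of each treatment cycle", but Table 2 places no laboratory or cardiac safety test at cycles 2 and 3.
- The active search can find results that exist. It cannot recover tests that were never done.
- Section 22 has all adverse events recorded and followed, so the toxicity itself would be known. That section governs collection; sections 20a and 20c govern who is analysed.

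**Group sizes and losses.** Section 14 gives 6 patients in phase I, taken here as 6 per disease group (the gastrointestinal total of 36 is 30 + 6). Phase II has 15 per gastrointestinal group and 28 newly diagnosed leukaemia patients.

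The gastrointestinal figure reproduces: (5² + 6²)(1.960 + 0.842)² / 6² = 13.3 per group, and 13.3 × 1.1 = 14.6, which rounds up to 15. Ten per cent of 30 is 3 patients, or 1.5 per group. Applying the same 10% to 28 is an assumption and gives 2.8, taken as 3.

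**Effect of exclusions.** The protocol states no toxicity rate, so all toxicity counts below are assumed. Brackets hold exact (Clopper-Pearson) 95% intervals.

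| Group | All treated | Patients with toxicity excluded | Patients without toxicity excluded |
|---|---|---|---|
| Phase I, 1 excluded | 2/6 = 33% (4 to 78%) | 1/5 = 20% (1 to 72%) | 2/5 = 40% (5 to 85%) |
| Phase I, 2 excluded | 2/6 = 33% (4 to 78%) | 0/4 = 0% (0 to 60%) | 2/4 = 50% (7 to 93%) |
| Gastrointestinal group, 1 excluded | 3/15 = 20% (4 to 48%) | 2/14 = 14% (2 to 43%) | 3/14 = 21% (5 to 51%) |
| Gastrointestinal group, 2 excluded | 3/15 = 20% (4 to 48%) | 1/13 = 8% (0.2 to 36%) | 3/13 = 23% (5 to 54%) |
| New leukaemia, 3 excluded | 6/28 = 21% (8 to 41%) | 3/25 = 12% (3 to 31%) | 6/25 = 24% (9 to 45%) |

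**General form.** Let p be the true proportion with toxicity, q the share excluded among patients with toxicity, and r the share excluded among the rest. The reported proportion is p(1−q) / [p(1−q) + (1−p)(1−r)]. With p = 0.20:

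- q = 0.5, r = 0: 0.10 / 0.90 = 0.111
- q = 0.5, r = 0.1: 0.10 / 0.82 = 0.122
- q = r: 0.200, no change
- q = 0, r = 0.1: 0.20 / 0.92 = 0.217
- q = 0.1, r = 0.5: 0.18 / 0.58 = 0.310

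The proportion falls only when patients with toxicity are excluded more often than the others.

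**The case against.** The strongest reply is that the rule is specific to each objective. For safety the relevant information is adverse events, and section 21b describes the phase I analysis in those terms. Section 22 monitors every subject and follows each event, so a patient who stops for toxicity already has what the safety objective needs. On that reading nobody with toxicity is lost. The reading is reasonable and probably what the investigators intend, but the protocol does not state it.

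Second, stopping treatment is not leaving the study. Weekly calls (11c), contact with relatives after missed visits (18b), a month of monitoring after treatment (30) and clinical visits at cycles 2 and 3 all make missing safety data less likely. In phase I the usual response to toxicity is a lower dose in the same patient, so losing both patients with toxicity would be extreme. This limits how often the problem would arise; it does not change who is analysed when it does.

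Third, the size is entirely assumed, the intervals overlap widely, and dose steps are untouched: they follow observed toxicity (for example "if there is no toxicity after 4 weeks, the dose will be increased to 2000 mg"), and the protocol sets no toxicity rate for the maximum tolerated dose. All of this stands.

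Fourth, a safety population is ordinary analysis-plan content, and its absence from an article would be no defect. But the point is not silence. The article states a rule for every objective, and an analysis plan that kept all treated patients could conflict with that rule as written.

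**Conclusion.** The concern holds as a point about a stated rule. Sections 20a and 20c apply complete-case analysis to every objective, safety is one of them, and nothing exempts it. Read literally, the rule can remove early stoppers from the safety analyses.

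The practical effect rests on three assumptions: that complete information is taken to mean the scheduled tests, that some patients miss those tests, and that those missing them differ in toxicity from the rest. Under the assumed counts, the phase I proportion could move from 33% to anywhere between 0% and 50%, a gastrointestinal group from 20% to between 8% and 23%, and the new leukaemia cohort from 21% to between 12% and 24%. If a recorded adverse event counts as complete, no patient with toxicity is lost. The change is worth making because it is cheap, but the selection of the maximum tolerated dose does not depend on it. Confidence in a material practical effect is moderate.

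**What to change.** - In sections 20a and 20c, limit the complete-information rule to the efficacy and quality-of-life objectives.
- In section 21b and for the phase II safety evaluations, state that safety is analysed in all patients who took at least one dose.
- Count each toxicity at the dose level where it arose, including in patients withdrawn before that level was finished.
- Let a missing scheduled laboratory or cardiac value affect only the summary of that test.
- Show exposure time beside the counts.

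The cost is wording only, since section 22 already has the events recorded. Patients who stop early for other reasons will enter the denominator with short exposure, which is why exposure time should be shown. The reported proportion may move in either direction.
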